## Abstract

**Background:**

Reviews of randomized controlled trials (RCTs) of cognitive behavioural therapy (CBT) for anxiety disorders have reported large pre- to post-treatment within-group effect sizes on measures of anxiety when supplied in therapist consultations and in technology-supported settings. However, the stringent experimental control of RCTs results in a lack of external validity, which limits the generalizability of findings to real-world frontline clinical practice. We set out to examine the specification of a protocol for study of the effectiveness of cell phone-supported CBT for in situ management of anxiety disorders.

**Methods and design:**

Nominal group methods were used for requirements analysis and protocol design. Making a distinction between different forms of technology-supported therapy, examination of therapists' role, and implementing trials in existing organizational and community contexts were found to be the central requirements in the protocol.

**Discussion:**

The resulting protocol (NCT01205191 at clinicaltrials.gov) for use in frontline clinical practice in which effectiveness, adherence, and the role of the therapists are analyzed, provides evidence for what are truly valuable cell phone-supported CBT treatments and guidance for the broader introduction of CBT in health services.

## Background

Ample evidence indicates that anxiety is under treated in western societies, and that large numbers of the population suffer needlessly. The World Health Organization (WHO) has estimated that 40% of disability attributed to anxiety reflects the fact that many potential anxiety patients never reach health care [1]. A major factor contributing to this shortcoming is that evidence-based psychotherapies are not practiced widely in community settings [2,3]. For instance, less than a quarter of those with anxiety disorders in the United Kingdom receive treatment of any sort [4]. In the United States, only about 40% of patients with mood or anxiety disorders receive any treatment [5]. It is in this context that expectations of cognitive behavioural therapy (CBT) are high. CBT methodology has the advantage of using well-defined treatment practices that can be easily taught to a variety of therapists and whose implementation can be monitored. Reviews of randomized controlled trials (RCTs) of CBT for anxiety disorders have reported large pre- to post-treatment within-group effect sizes on measures of anxiety when supplied in therapist consultations [6,7], in computer-supported sessions at practices [8,9], and over the Internet [10,11]. In Sweden, CBT is the current treatment of choice for mild to moderate anxiety disorder [12].

Despite its proven efficacy, CBT still seems to be neglected in practice settings. In this study, we address 2 possible reasons for this situation. The first is that most of the research has been conducted using samples with isolated (rather than comorbid) disorders, but most therapists help individuals with multiple comorbid problems. It is not known if CBT techniques adapted to a particular client's needs by a skilled therapist in a community setting achieve a better result than a therapist following a structured routine. It does seem that experienced therapists prefer to select from a variety of techniques rather than to follow a regimented program. Moreover, patient non-adherence is a persistent and complex phenomenon in frontline CBT practice [13]. The refractory nature of this problem is reflected by the fact that a large proportion of non-adherence has come to be routinely accepted when planning interventions. Critics argue that RCTs' stringent experimental controls (e.g. patients with homogenous diagnoses and highly trained and supervised therapists) result in a lack of external validity, which limits the generalizability of findings to real-world or frontline clinical practice [14,15]. In addition, studies of the effectiveness of CBT for anxiety disorders have consistently reported lower patient adherence than RCTs [13,16].

The second possible reason for under utilization is that a fundamental principle in CBT is to document and adjust behaviour and thought processes when and where they occur. Accordingly, a goal in developing novel applications of CBT should be to assist therapy in situ, that is, exactly when it is needed. Using participatory design methods, we have developed a set of such applications [17]. In this process, we acknowledge that adherence to mental health services is no longer only a matter of complying with a decided course of treatment in a clinical setting, but of reaching, connecting to, motivating, and sharing health decisions with patients and populations (Figure 1). The perspective on health service provision thereby shifts from biomedicine to infomedicine; patients and health workers join in informed, shared decision-making and governance [18].

**Figure 1 F1:**
[figure not shown]
**Health service perspective on non-adherence to CBT for anxiety disorders**.

We conclude that there is a need to examine carefully the external validity and effectiveness of CBT treatments for anxiety that have already been shown to be efficacious, and to identify factors that reduce non-adherence. In this study, we used these presumptions to plan for the examination of a new generation of CBT programs. With this understanding, we set out to define a protocol for examination of the effectiveness of cell phone-supported CBT for anxiety disorders in frontline settings that also allows to evaluate adherence to therapy. Specifically, the aims of this study were to define a protocol for assessment of

• the superiority of cell phone-supported CBT (CBT-cell phone) treatment against anxiety disorders compared with CBT treatment as usual (CBT-TAU), and

• adherence with CBT-cell phone compared with CBT-TAU and CBT provided with access to a placebo technical device (CBT-placebo).

## Methods and design

Nominal group methods [19] were used for requirements analysis and protocol design (Figure 2). Two expert panels examined requirements on the data to be collected: a technical design panel (*n *= 5) with a background in computer science and cognitive science, and a therapy panel (*n *= 4) consisting of practising therapists. The requirements data collected were transferred to a study protocol design panel (*n *= 6) with a background in social medicine, general practice, CBT practice, health informatics, and cognitive science.

**Figure 2 F2:**
[figure not shown]
**Flow of study protocol specification and development of requirements during the formulation process**.

### Requirements data collection

The task communicated to the therapy panel was to make sure the protocol conformed to organizational and therapeutic routines and content. The task communicated to the technical design panel was to make sure that the protocol conformed to present cell phone technology and limitations. In addition, the technical design panel, in cooperation with the therapy panel, developed a specification of the technical systems to ensure that, in accordance with the protocol, the content of the technical solution was compatible with the paper-based homework used in present CBT for anxiety syndrome.

### Requirements data analysis

The data from the study requirement analysis were transferred to a protocol specification by the study protocol panel. The specification was developed during a series of meetings lasting for 2 hours each (*n *= 8) at which the study protocol, technical design, and therapy methods in use were systematically developed and discussed. The specification was finally refined at separate meetings with the therapy and technical design panels.

### Study protocol requirements

The results of the requirement analysis yielded 3 requirement areas that were found to be important when studying the effectiveness and adherence to cell phone-supported CBT in a community context.

### Effectiveness trials

Even if different forms of CBT have been shown to be efficacious in RCTs, therapy provided in a community setting entails a wider variety of patient problems and comorbidity. A recent meta-analytic review of CBT supported by or delivered through information technology (IT) found no significant differences between face-to-face and computer-aided psychotherapy for anxiety and no differences between the system used (PC, palmtop, other) [20]. However, many studies of computer-aided CBT have used small samples. It is also a concern that most studies of computer support in CBT lack details on therapist contacts, time spent on assessment and diagnosis, and sparse reports of interventions delivered by ordinary therapists [21]. When introducing cell phone support in therapy in front-line settings, it is therefore important to be specific regarding what is compared, and to provide a large enough sample to be able to determine differences in effectiveness.

### The role of the therapist

Another important issue in effectiveness evaluations of IT-supported therapy is non-adherence. In RCTs of computer-supported CBT, different methods have been used to deal with dropouts (e.g. including only completers) [20]. Based on the evidence from the RCTs reported, it is tempting to meet the growing demand for CBT with computer-based therapy programs. However, although effective computer-based treatments have been tailored for specific and well-diagnosed patients, in practice there is a substantial comorbidity between anxiety and other mental illnesses, and the therapists variable in this context is still not well understood [21,22]. Tailoring of Internet therapies according to diagnostic profiles may be possible; however, visitors to therapy web sites who have registered on their own initiative have also had larger dropout rates than that reported in RCTs [23].

### Organizational and community context

To examine the effectiveness rather than the efficacy of CBT, it is important to include comorbid disorders and base the study on total populations. Reviews of RCTs of CBT for anxiety disorders have reported large pre- to post-treatment within-group effect sizes on measures of anxiety when supplied in therapist consultations in computer-supported sessions at practices [8,9] and on the Internet [10,11]. Yet, effective dissemination of evidence-based intervention to community stakeholders has been shown to be challenging [24]. Facing the difficulties of closing the gap between research and practice, the UCLA/RAND NIMH Center has developed a framework to assess the relevant contextual factors, identify, develop and evaluate new strategies, provide useful formative feedback, develop capacity among stakeholders and to meaningfully generalize findings. Evidence on dissemination and implementation in an organizational and community context rests on process evaluation of contextual factors, stages of diffusion, and outcome of interventions [24]. A successful outcome in one implementation is only anecdotal evidence, unless some evaluation of the context (structure and process) and adaptations made for the context are also documented.

### Study protocol

The final protocol (NCT01205191 at clinicaltrials.gov) informed by the data analysis was developed with regard to the observed limitations of earlier studies of computer-supported CBT; e.g. the substantial dropout rates, partial neglect of therapist involvement, and lack of direct comparisons between face-to-face and IT-supported methods [21]. The protocol is presented as it is implemented in a study at the Unga Vuxna (Young Adults) clinic in Östergötland County, Sweden.

### Study setting

The Unga Vuxna service accepts clients aged 18-25 years from a total population in a region in southern Sweden (*n *= 20,000) following a therapist telephone triage (Figure 3). All therapists (clinical psychologists, social workers) have a two-year (certified) academic training in CBT. The intervention at Unga Vuxna consists of 6 CBT sessions, each lasting 45 minutes. Sessions follow a predefined program, but are also customized to the patient's specific needs, including initial assessment whether the patient has expressed any suicidal intent. Clients also continue to receive pharmacotherapy if previously prescribed by their physician. A report of the patient's progress, including whether the patient has expressed any suicidal intent, is recorded. Homework projects are generated for each patient, to be accomplished before the next session. A report of the patient's progress is recorded and all clients are followed up by a visit at the clinic 3 months after the therapy has been concluded.

**Figure 3 F3:**
[figure not shown]
**Overview of the population offered the Unga Vuxna service in Östergötland, Sweden**.

### Study inclusion criteria

The inclusion criteria are: (1) age 18 to 25 years and (2) scoring 7 or higher on the anxiety section of the Hospital Anxiety and Depression Scale (HAD) at initial evaluation. Clients are excluded if they: (1) display symptoms at the initial evaluation that suggest referral to a psychiatric specialist, e.g. active suicidal ideas or symptoms of a psychotic disorder, organic mental disorder or alcohol and/or drug dependence or (2) are unable to read, write or speak Swedish.

### Study performance

#### Treatments

Clients receive whatever treatment their therapist prescribes. To replicate natural conditions, interventions received by clients are not constrained by the study. The interventions thus also include, for example, provision of practical/social support at the employment office, and further medical investigations.

#### Procedures

The procedure follows the intention to treat (ITT) principle, that is, based on the initial treatment intent, not on the treatment eventually administered. The Unga Vuxna service accepts clients following a therapist telephone triage. Recruitment to the study is administered in association with the first CBT session at the clinic. At this session, routine screening is performed by administrating the Hospital Anxiety and Depression Scale (HADS) to clients. Individuals found fitting the study criteria are presented with information materials about the study by a study nurse. The materials are made available to the client for evaluation in private without the therapist being present. The allocation schedule is generated by a biostatistician outside the clinic before the study commences using an individual unit of randomization. Individuals who fit the inclusion criteria and have consented to participate are stratified according to whether they are prescribed medication or not (yes, no) and with regard to their HADS-D score. They are then randomly allocated to receive CBT-cell phone, CBT-TAU, or CBT-placebo (Figure 4). To parallel the IT-lending situation in the CBT-cell phone strand (in adherence analyses), the clients allocated to CBT-placebo are provided with an MP3-player with anti-stress materials to use between the sessions. The sealed envelopes are opened in strict numerical sequence by the study nurse. The nurse is instructed to spend no more than 10 minutes before and after each session with each client.

**Figure 4 F4:**
[figure not shown]
**Study procedures**. The average treatment period at Unga Vuxna is 3 months.

#### Study outcome measures

The primary outcome measure is the Beck Anxiety Inventory [BAI]. The BAI [25] is a 21-item symptom checklist rated on a 4-point scale (0-3). The main secondary set of outcome measures describes patient adherence. Data on adherence are collected in 4 dimensions from the therapists after the last session; that is whether the client has

• discontinued the CBT program by not showing up at sessions;

• discontinued the CBT program by actively informing the therapist;

• been discontinued from the treatment by the therapist; and

• not fulfilled the therapeutic contract, e.g. by not completing homework agreed upon.

The remaining secondary outcome measures are HADS-A and -D, and the General Health Questionnaire [GHQ-12]. The outcome measures are administered on each of 3 occasions: pre-treatment, when the participants had completed their programme, and with follow-up at 6 months. The GHQ has demonstrated validity with young adults (17+ years) from the United Kingdom [26]. The sensitivity and specificity for both HADS-A and HADS-D are similar to the sensitivity and specificity achieved by the GHQ and they perform well in assessing the symptom severity of anxiety disorders and depression in both somatic, psychiatric and primary care patients, and in the general population [27].

### Statistical analysis

Power calculations were performed to determine the minimum sample size needed to fulfil the research aims. The calculations were based on change scores (pre- to post-treatment) between groups in 2 previous studies comparing CBT as usual with CBT supported by handheld computers [28] and CBT provided by stationary surgery-located computers [9]. To detect a standard deviation difference of 0.3 in BAI change scores at 80% power and with 0.05 alpha, we determined that a total sample size close to 150 per stand (450 in total) was needed.

For each of the outcome measures, a series of mixed effects models will be considered. Such models are described in detail by Everitt and Pickles [29]. Model adjustments will be used to analyse associations between pre- and post-randomization values of outcome (i.e. post-CBT and 6 months follow-up), treatment, drugs, and parallel depression. For dimensional outcomes (anxiety scores), ITT analyses will be conducted using all participants enrolled in the study, and the last available data point will be used as the post-treatment score. Uncontrolled effect sizes will be calculated for pre- to post-treatment change. For categorical outcomes (adherence), treatments will be compared using Pearson's chi-square test, Fisher's exact test, or logistic regression, as appropriate.

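### At two-sided 0.05, 150 per arm gives about 74% power, not the stated 80%, for 0.3 SD of BAI change, and the plan does not fix the deciding contrast as baseline-adjusted

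*Protocol article*

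**What the plan says.** The aims at the end of the Background make superiority of CBT-cell phone over CBT-TAU the first objective. Under Study outcome measures, the BAI is primary and is collected before treatment, at programme completion and at 6 months.

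The Statistical analysis section describes the sizing as follows: "The calculations were based on change scores (pre- to post-treatment) between groups in 2 previous studies". The target is given in the same unit: "To detect a standard deviation difference of 0.3 in BAI change scores", "at 80% power and with 0.05 alpha". The result is "a total sample size close to 150 per stand (450 in total) was needed". The section does not say whether the test is one- or two-sided and gives no pre-post correlation.

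For the analysis, the section says that a series of mixed effects models will be considered for each outcome. On the role of baseline it says: "Model adjustments will be used to analyse associations between pre- and post-randomization values of outcome", and it lists treatment, drugs and parallel depression alongside. For anxiety scores it adds: "ITT analyses will be conducted using all participants enrolled in the study, and the last available data point will be used as the post-treatment score". It does not single out one model or contrast as the one that decides superiority.

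**The concern.** There are two linked problems.

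First, the one sentence that attaches a target, an alpha and a power to the primary comparison does not hold at the usual two-sided level. A reader would take 150 per arm as enough for 0.3 SD of change, and on that reading it is not.

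Second, the sized quantity and the modelled quantity may differ. Sizing uses the difference in change scores. The modelling sentence could mean post-treatment BAI given pre-treatment BAI. It could equally mean a mixed model with all occasions as outcomes and a time-by-treatment term; with complete data and no constraint on the baseline means, that contrast is simply the difference in mean change. The two estimators have different standard errors. Raw change subtracts the whole baseline and so carries baseline noise unless the pre-post correlation is close to 1. In a randomised comparison the baseline-adjusted contrast is unbiased and, in large samples, never less precise. If the choice stays open, precision on the primary outcome can be lost even though the baseline has already been measured.

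In addition, 0.3 SD of change is not a fixed number of BAI points, because the SD of change depends on the correlation.

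**Working it through.** **Inputs.** From the Statistical analysis section: difference 0.3 in SDs of BAI change, alpha 0.05, power 80%, about 150 per arm. Assumed because not stated: two-sided test, equal pre and post SDs (σ), pre-post correlation r as a range, and no multiplicity adjustment for the single CBT-cell phone versus CBT-TAU contrast.

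**1. The plan's own figure.** n per arm = 2(z_alpha + z_beta)²/d².
- Two-sided: 2(1.960 + 0.842)²/0.09 = 174.4, so 175 per arm.
- One-sided: 2(1.645 + 0.842)²/0.09 = 137.4, so 138 per arm.

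Power at 150 per arm uses d·√(n/2) = 0.3 × √75 = 2.598.
- Two-sided: Φ(2.598 − 1.960) = 73.8% (73.6% by noncentral t).
- One-sided: Φ(2.598 − 1.645) = 83.0%.

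Other readings fit no better. Bonferroni for two or three contrasts needs 212 or 233 per arm. A three-arm global test at 450 has 63.5% power with means 0, 0.15, 0.3 and 76.8% with means 0, 0, 0.3. The two-sided difference detectable with 80% power at 150 per arm is 2.802 × √(2/150) = 0.323.

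**2. Baseline-adjusted contrast, same clients.** Change has variance 2σ²(1 − r). Post-treatment BAI given pre-treatment BAI has residual variance σ²(1 − r²). The ratio is (1 + r)/2, so the effective difference is 0.3/√((1 + r)/2).

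| r | variance ratio | effective d | power at 150 per arm | n per arm for 80% | 0.3 change-SDs in raw BAI SDs, 0.3√(2(1 − r)) |
|---|---|---|---|---|---|
| 0.3 | 0.65 | 0.372 | 89.7% | 114 | 0.35 |
| 0.5 | 0.75 | 0.346 | 85.1% | 131 | 0.30 |
| 0.7 | 0.85 | 0.325 | 80.5% | 149 | 0.23 |
| 0.8 | 0.90 | 0.316 | 78.2% | 157 | 0.19 |

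Noncentral t gives 89.5%, 84.9%, 80.2% and 77.9%. Simulation (6,000 runs each at r = 0.3, 0.5, 0.7) gives 89.6%, 84.8% and 79.8% for the adjusted contrast, and 74.2%, 74.0% and 72.9% for raw change. Adjusted power drops below 80% above r of about 0.72.

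**3. Effect of carrying values forward.** The BAI is measured only before treatment, at completion and at 6 months, so a client who leaves before completion has only the baseline to carry forward. Take an illustrative 20% of such clients (the documents give no rate) and no mean change over time.
- The mean difference becomes 0.8 × 0.3 = 0.24 and the variance of change becomes 0.8, so d = 0.24/√0.8 = 0.268. Raw-change power is Φ(0.268 × √75 − 1.960) = 64%.
- The overall correlation becomes r′ = 0.8r + 0.2. Dividing 0.268 by √((1 + r′)/2) gives d = 0.316, 0.300 and 0.286 for completer r = 0.3, 0.5 and 0.7, hence power of 78%, 74% and 70%.

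**The case against.** The strongest reply is that the article never says superiority will be decided on change scores. Apart from the power calculation, change appears only in the uncontrolled pre-to-post effect sizes, which are within-group descriptions. The modelling sentence puts the pre-randomization value in the same models as treatment, and loosely worded baseline adjustment is a natural reading of it. Sizing on change because the earlier studies reported change, then analysing with a more efficient model, is ordinary practice and costs no precision. This stands. A reader might infer that the plan commits to a change-score test; the document does not support that, and the planned models may already capture some or all of the gain. What the wording does not do is settle the matter, since it fits both contrasts.

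A second reply is that the exact model belongs in a fuller document. That is fair for covariate lists and covariance structures. It does not cover the sample-size sentence, which is stated here and does not hold two-sided.

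A third is that 0.3 may be a rounded 0.32, which would make 150 per arm about right. That is possible, but the text does not say so, and at the printed 0.3 the power is 74%. A one-sided test would also reach 80%, but none is stated.

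A fourth is that the gain from adjustment depends on assumptions. This stands too. A reader might infer that adjustment secures at least 80% power. It does so only for r up to about 0.72 with no dropout. If 0.3 were meant in raw BAI SDs, adjusted power would be 77.7%, 85.1% and 95.3% at r = 0.3, 0.5 and 0.7, so the dependence on r would reverse. Restating the sizing with a correlation also invites choosing one that makes 150 fit, so the value needs justifying in advance.

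**Conclusion.** The point holds in two parts. On the stated basis, the stated 80% power is about 74% at two-sided 0.05, a shortfall of 25 clients per arm (175 against 150); sidedness is unstated, and one-sided power would be 83%. Separately, the text leaves open whether the deciding BAI contrast is baseline-adjusted.

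Fixing it as adjusted cuts the contrast's variance by 35% to 10% for r from 0.3 to 0.8. At r = 0.7 this does no more than restore the power the article already claims. The absolute figures rest on equal SDs, a target in change-score SDs, a two-sided test, complete data and an r that the documents do not give. Dropout with baseline carried forward lowers them, but in the 20% illustration adjustment still beats raw change. The large-sample advantage of adjustment over raw change does not depend on which r is right.

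**What to change.** Make two wording changes in the Statistical analysis section.

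1. State that aim 1 is decided by the CBT-cell phone minus CBT-TAU difference in post-treatment BAI, from a model with pre-treatment BAI as a covariate.
2. Restate the sample-size sentence with the sidedness, the target in BAI points, and the power delivered at 150 per arm. That is either about 74% on change scores (two-sided) or the adjusted figure for a pre-post correlation justified in advance. Show a range of correlations and an allowance for clients without a post-treatment value.

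No new data, visits or clients are needed, because pre-treatment BAI is already collected. The cost is that a correlation must be assumed and defended, and that the stated 80% may have to be revised.

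### The sample-size statement does not agree with itself: at two-sided 0.05, 150 per arm gives about 74% power for 0.3 SD in BAI change, not 80%

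*Protocol article*

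**What the plan says.** The calculation is in the Statistical analysis section of the protocol article. The effect is given as "To detect a standard deviation difference of 0.3 in BAI change scores". The error rates and the number per arm are given as "in BAI change scores at 80% power and with 0.05 alpha, we determined that a total sample size close to 150 per stand", with 450 as the total over the three arms. The basis is described as follows: "The calculations were based on change scores (pre- to post-treatment) between groups in 2 previous studies". The article presents the result as the minimum needed for the research aims.

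The aims at the end of the Background make CBT-cell phone against CBT-TAU the effectiveness comparison. The CBT-placebo arm is named only in the adherence aim. The Study outcome measures section makes BAI the primary outcome. Nothing says whether the 0.05 is one-sided or two-sided.

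For the analysis itself, the same section plans mixed effects models that relate pre- and post-randomization values of the outcome to treatment, drugs and depression. All enrolled clients are kept, with the last available value used as the post-treatment score.

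**The concern.** The article prints the effect size, alpha, power and number per arm together, so the calculation can be checked without any other document. On the usual reading (two arms, change scores, two-sided 0.05) the four values cannot all be true: 150 per arm is about 26 short of the 176 that 80% power requires.

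This calculation justifies the sample size for the primary outcome and the first aim. A reader of a null BAI result would take the chance of having missed a 0.3 SD difference to be 20%. On the test that the calculation describes, that chance is about 26%. The article itself criticises earlier computer-aided CBT studies for small samples and asks for a sample large enough to detect differences, so the printed power will be relied on.

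**Working it through.** **Inputs from the Statistical analysis section:** difference d = 0.3 in units of the SD of BAI change; alpha 0.05; power 80%; 150 per arm, three arms, 450 in total (equal allocation). **Assumed:** two-sided test, since sidedness is not given.

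**1. Number needed, two-sided.**
n per arm = 2 × (z₀.₉₇₅ + z₀.₈₀)² / d² = 2 × (1.960 + 0.842)² / 0.3² = 174.4, so 175.
The noncentral t gives 175.4, so 176. The total for three arms is 525 to 528. The stated 150 is not reproduced.

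**2. Power at 150 per arm, two-sided.**
Standardised difference = 0.3 / √(2/150) = 2.598.
Power = Φ(2.598 − 1.960) = 0.738. The noncentral t gives 0.736. The miss rate is therefore 1 − 0.736 = 0.264.

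**3. Difference detectable with 80% power at 150 per arm.**
(1.960 + 0.842) × √(2/150) = 0.3235 SD. The noncentral t gives 0.325 SD.

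**4. Other readings that might explain 150.**

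| Reading | Needed for 80% | Power at 150 per arm |
|---|---|---|
| One-sided 0.05, two arms | 138 per arm (t: 139) | 83% |
| Three-group F test, one arm differs by 0.3 | 485 in total | 76.8% |
| Three-group F test, means 0, 0.15, 0.3 | 645 in total | 63.5% |
| Two-sided, Bonferroni for 2 comparisons | 212 per arm | 63.9% |
| Two-sided, Bonferroni for 3 comparisons | 233 per arm | 58.1% |
| CBT-cell phone against both comparators pooled | 131 in the cell phone arm | 85.1% |

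With equal whole-number arms, the two F-test totals become 3 × 162 = 486 and 3 × 216 = 648. None of these readings gives 150 per arm.

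**5. Baseline-adjusted analysis.** Let ρ be the correlation between pre- and post-treatment BAI, which the article does not give. If 0.3 is in change-score SD units, adjustment multiplies the variance by (1 − ρ²) / [2(1 − ρ)] = (1 + ρ)/2. The effective difference is therefore 0.3 / √((1 + ρ)/2).

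| Assumed ρ | Effective d | Power at 150 per arm (normal / t) |
|---|---|---|
| 0.5 | 0.346 | 85.1% / 84.9% |
| 0.6 | 0.335 | 82.8% / 82.5% |
| 0.7 | 0.325 | 80.5% / 80.2% |
| 0.72 | 0.323 | 80.0% / 79.7% |

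These figures assume complete data. At ρ = 0.7 the number needed is 149 per arm, close to the stated 150. However, the article says that the calculation used change scores and gives no correlation.

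**The case against.** **Sidedness.** The article gives only 0.05, and the aim is worded as superiority. If a one-sided 0.05 test was meant, 150 per arm exceeds the 80% target. This stands as far as it goes: the shortfall depends on the conventional two-sided reading. But one-sided testing does not yield 150, and no one-sided test is stated.

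**The planned model is not a change-score t-test.** The mixed models bring in pre-treatment values, and step 5 shows at least 80% power at 150 per arm for ρ up to about 0.7. This also stands. A reader might infer that the trial is underpowered; the article does not support that. What fails is the printed change-score calculation, and the 26% miss rate belongs only to an unadjusted two-sided test.

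**Routes to 150.** A reader might also infer that 150 can come only from a one-sided 5% test. That is not so. That test needs 138 to 139, and about 150 is reached by other routes, such as one-sided with roughly 8% loss (138 / 0.92 = 150) or adjustment with ρ near 0.7. Each needs an input that the article does not give.

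**Dropout.** It is tempting to add that the sample size ignores expected dropout. The article does not support this. Its remarks on "the substantial dropout rates, partial neglect of therapist involvement" and that "studies of the effectiveness of CBT for anxiety disorders have consistently reported lower patient adherence than RCTs" describe earlier research, and the second concerns adherence rather than loss of outcome data. No dropout rate is given for this trial. All enrolled clients stay in the analysis through their last available value, so the analysed number would remain 150 per arm. An inflation allowance may also be left to the full protocol.

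**Size.** The gap is about 6 points of power, for a number hedged as approximate. That is modest, but 150 is some 15% below 176, which the hedge does not cover.

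**Conclusion.** The sample-size statement is wrong as written. For 0.3 SD in BAI change between two arms at two-sided 0.05, 80% power needs about 176 per arm. The stated 150 gives about 74%, and detects 0.325 SD at 80% power. This rests on one assumption, the two-sided test. If the test is one-sided at 0.05, 150 is sufficient (83%) but still does not match the 138 to 139 required.

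The finding is confined to the printed figures. Whether the planned baseline-adjusted model has 80% power depends on a pre-post correlation that the article does not state.

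**What to change.** In the Statistical analysis section, state the sidedness of the 0.05 and make the number, power and difference agree. On the two-sided reading, the statement would be that 150 per arm gives about 74% power to detect 0.3 SD on unadjusted BAI change scores for CBT-cell phone against CBT-TAU, or 80% power for 0.325 SD. If a one-sided test was intended, say so and give the matching figures (138 to 139 per arm for 80%, or 83% at 150).

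If the sponsor relies on the baseline-adjusted model to support 450 clients, state its power under a named pre-post correlation. With complete data, an assumed 0.5 gives about 85% and an assumed 0.7 about 80%.

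The cost is a change of wording. No extra enrolment is needed, and no outcome, allocation or analysis changes. On unadjusted change scores with a two-sided test, the stated power becomes less favourable.
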